## 1 Data sources

### 1.1 The Chronic Disease Management Program Minimum Data Set

The analysis will include every participant recorded in the program minimum dataset and enrolled between January 2011 and December 2013. The date of enrolment will be calculated using the following approach: If the Program consent date is available, it will be used as the enrolment date. If it is missing, and the Enrolment decision date is available, then this date will be used. If this is also not available, then the Registration date will be used as enrolment date instead.

### 1.2 APDC

The APDC dataset will contain every public and private hospital admission which occurring between January 2007 and December 2013 in NSW. CDMP participants will be flagged.

### 1.3 EDDC

The APDC dataset will contain every public and private emergency department admission occurring between January 2007 and December 2013 in NSW. CDMP participants will be flagged.

### 1.4 Registry of birth, deaths and marriages (RBDM)

The RBDM dataset will contain every death recorded in NSW between January 2007 and December 2013 in NSW. CDMP participants will be flagged.

## 2 Subject disposition and baseline characteristics

### 2.1 Subject Disposition

A bar chart will show the number of patient registrations in the CDMP outcomes register by 6-month period for the entire duration of the program i.e. between January 2009 and December 2013.

### 2.2 Description of CDMP participants

We will describe baseline characteristics of CDMP participants overall and broken down by year of enrolment (2011, 2012 and 2013). Baseline characteristics will include:

- Age
- Gender
- Aboriginality
- ARIA
- SEIFA

- Source of referral
- Target condition(s)
- Risk of hospitalisation
- Special population flag
- Initial SF1
- Initial intervention
- Reasons for non-enrolment
- Referral target
- Program consent
- Data use consent
- Number of hospitalisations in 2010, average length of hospital stay, total hospital bed days
- Number of unplanned hospitalisations in 2010, average length of unplanned hospital stay, total unplanned hospital bed days
- Number of avoidable hospitalisations in 2010, average length of avoidable hospital stay, total avoidable hospital bed days
- Number of ED admissions in 2010 overall and by triage categories 1-5

### 3 Evaluation of efficacy outcomes

#### 3.1 Efficacy outcomes

The primary efficacy outcome will be the rate of avoidable hospitalisations. Avoidable hospitalisations are defined as hospitalisations that fall under any of the following categories:

1. Vaccine-preventable:
  - "Influenza and pneumonia" (where any of the diagnosis fields have ICD-10-AM code as J10, J11, J13, J14, J15.3, J15.4, J15.7, J15.9, J16.8, J18.1, J18.8 excluding those where secondary diagnosis is D57)
  - "Other preventable vaccine" (where any of the diagnosis fields have ICD-10-AM code as A35, A36, A37, A80, B05, B06, B16.1, B16.9, B18.0, B18.1, B26, G00.0, M01.4)
2. Chronic:
  - "Diabetes complications" (where any of the diagnosis fields have ICD-10-AM code as E10.1-E10.8, E11.0-E11.8, E13.0-E13.8, E14.0-E14.8)
  - "Nutritional deficiencies" (where principal diagnosis has ICD-10-AM code as any of E40-E43, E55.0, E64.3)
  - "Iron deficiency anaemia" (where principal diagnosis has ICD-10-AM code as any of D50.1-D50.9)
  - "Hypertension" (where principal diagnosis has ICD-10-AM code as any of I10, I11.9)
  - "Congestive heart failure" (where principal diagnosis has ICD-10-AM code as any of I11.0, I50, J81)
  - "Angina" (where principal diagnosis has ICD-10-AM code as any of I20, I24.0, I24.8, I24.9)
  - "Chronic obstructive pulmonary disease" (where principal diagnosis has ICD-10-AM code as any of J41-J44, J47 or the principal diagnosis ICD-10-AM code is J20 with secondary diagnosis as J41, J42, J43, J44, J47)

- "Asthma" (where principal diagnosis has ICD-10-AM code as any of J45, J46)
3. Acute:
- "Dehydration and gastroenteritis" (where principal diagnosis has ICD-10-AM code as any of E86, K52.2, K52.8, K52.9)
  - "Convulsions and epilepsy" (where principal diagnosis has ICD-10-AM code as any of G40, G41, O15, R56)
  - "Ear, nose and throat infections" (where principal diagnosis has ICD-10-AM code as any of H66, H67, J02, J03, J06, J31.2)
  - "Dental conditions" (where principal diagnosis has ICD-10-AM code as any of A69.0, K02-K06, K08, K09.8, K09.9, K12, K13)
  - "Perforated/bleeding ulcer" (where principal diagnosis has ICD-10-AM code as any of K25.0-K25.2, K25.4-K25.6, K26.0-K26.2, K26.4-K26.6, K27.0-K27.2, K27.4-K27.6, K28.0-K28.2, K28.4-K28.6)
  - "Ruptured appendix" (where any of the diagnosis fields have ICD-10-AM code as K35.0)
  - "Pyelonephritis" (where principal diagnosis has ICD-10-AM code as any of N10, N11, N12, N13.6)
  - "Pelvic inflammatory disease" (where principal diagnosis has ICD-10-AM code as any of N70, N73, N74)
  - "Cellulitis" (where principal diagnosis has ICD-10-AM code as any of L03, L04, L08.0, L08.8, L08.9, L88, L98.0, L98.3)
  - "Gangrene" (where any of the diagnosis fields have ICD-10-AM code as R02)

Secondary efficacy outcomes will include:

1. Unplanned hospitalisations defined as hospitalisations that have status of "emergency" or the mode of separation is not "Transfer to Palliative Care Unit / Hospice" or any of the secondary diagnoses are not "Palliative care "(Z51.5)".
2. Hospital re-admissions defined as admissions occurring less than 30 days after discharge
3. Emergency department admissions
4. Deaths
5. Number of hospital bed-days

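### Primary outcome: five any-field categories with no same-day exclusion let unrelated and repeat-treatment admissions, chiefly those carrying diabetes codes, count as avoidable events

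*SAP*

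**What the plan says.** SAP section 3.1 states: "The primary efficacy outcome will be the rate of avoidable hospitalisations". The categories are combined by a simple either-or rule: "Avoidable hospitalisations are defined as hospitalisations that fall under any of the following categories".

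Five categories accept the code in any diagnosis field of the admission:
- influenza and pneumonia ("where any of the diagnosis fields have ICD-10-AM code as J10, J11, J13, J14" and further codes), with one exclusion, a secondary D57;
- other vaccine-preventable conditions ("where any of the diagnosis fields have ICD-10-AM code as A35, A36, A37, A80, B05, B06, B16.1, B16.9, B18.0, B18.1, B26, G00.0, M01.4");
- diabetes complications ("where any of the diagnosis fields have ICD-10-AM code as E10.1-E10.8, E11.0-E11.8, E13.0-E13.8, E14.0-E14.8");
- ruptured appendix (K35.0);
- gangrene ("where any of the diagnosis fields have ICD-10-AM code as R02").

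Every other category requires the principal diagnosis. COPD also admits a principal J20 when a listed secondary code is present.

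On the source data, section 1.2 says: "The APDC dataset will contain every public and private hospital admission". Neither section sets aside planned or same-day stays. Emergency status is used only in the secondary outcome of unplanned hospitalisations. Under the heading Analysis of matched data (section 3.3.1), the outcome is an event rate, so each repeat admission counts. The number of avoidable hospitalisations in 2010 is a candidate covariate in section 3.2.4 and, through Step 3 of the matching procedure, a propensity-score variable.

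**The concern.** The principal diagnosis stands for the reason for admission. An additional diagnosis may only record a condition that the patient also has. For a long-term condition such as a diabetic complication, and possibly chronic hepatitis B (B18.0, B18.1), the any-field rule lets an admission for an unrelated reason count as avoidable if the code is on that record. If someone attends repeatedly for same-day treatment, and each session is an admission carrying the code, each session is an event.

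Three things are at stake. Events that the program cannot prevent pull the rate ratio towards 1. A few very frequent attenders can dominate both the mean and its standard error. A small difference between groups in the share of such people can look like a program effect in either direction. All three bear on the primary matched analysis, and the same rule shapes the 2010 covariate used in matching and adjustment.

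For influenza and pneumonia, ruptured appendix and gangrene the issue is mostly single admissions for other reasons, not repeated sessions.

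**Working it through.** The SAP states no event rate, count, power or effect size, so it has no figure of its own to reproduce. The text gives the mechanism; the arithmetic only shows how large it could be.

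**Assumed inputs, none from the SAP**
- m = 156 same-day sessions a year (three a week, as for dialysis), each recorded as an admission with a listed diabetes code as an additional diagnosis.
- f = 0.5% of people are such attenders, in both groups.
- b = 0.5 other avoidable admissions per person-year, range 0.2 to 1.0, with person-level variance b + 2b².
- True rate ratio for those other admissions 0.80; sessions unaffected by the program.

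**1. Share of events.** Added rate = m·f = 156 × 0.005 = 0.78 per person-year. Share = 0.78 / (b + 0.78).
- b = 0.5: 0.78 / 1.28 = 61%
- b = 1.0: 0.78 / 1.78 = 44%
- b = 0.2: 0.78 / 0.98 = 80%

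**2. Dilution.** Observed ratio = (0.8b + 0.78) / (b + 0.78).
- b = 0.5: 1.18 / 1.28 = 0.92
- b = 1.0: 1.58 / 1.78 = 0.89
- b = 0.2: 0.94 / 0.98 = 0.96

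**3. Precision.** Variance with sessions = f(1 − f)m² + mf + b + 2b². At b = 0.5 this is 121.07 + 0.78 + 1.00 = 122.85, against 1.00 without sessions. The SE of the log rate is proportional to SD divided by mean: √122.85 / 1.28 = 8.66 with sessions and √1.00 / 0.5 = 2.00 without, a ratio of 4.3. At b = 0.2 the ratio is also 4.3, and at b = 1.0 it is 3.6.

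**4. Dilution without assuming dialysis.** If a share s of control-group events is unrelated to the program for whatever reason, the observed ratio is s + (1 − s) × 0.80. For s = 10%, 25%, 50% and 75% this gives 0.82, 0.85, 0.90 and 0.95. The information needed, (ln 0.80 / ln observed)², rises about 1.3-, 1.9-, 4.5- and 19-fold.

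**5. Imbalance.** Take no program effect, f = 0.5% in one group and 0.35% in the other, b = 0.5. The ratio is (0.5 + 0.78) / (0.5 + 0.7 × 0.78) = 1.28 / 1.046 = 1.22 (1.15 at b = 1.0, 1.31 at b = 0.2). This models no matching. Would the Step 6 balance check flag it? If the same difference were present in the 2010 count, the mean difference would be 1.28 − 1.046 = 0.234. The two variances are 122.85 and 86.42 (84.88 + 0.55 + 1.00, rounded), so the pooled SD is √104.6 = 10.2 and the standardised difference is about 0.02. That would look well balanced.

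**The case against.** The strongest reply is that nothing here is shown to happen. The SAP does not mention dialysis or any same-day treatment, does not say how such sessions are recorded, and gives no counts. Every input above is assumed, and steps 1 to 3 and 5 concern only codes likely to recur across sessions. This stands. A reader might infer that the primary rate is swamped; the document supports only that the rule permits it.

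Second, the definition is explicit and can be programmed. The field rule is set category by category, with a D57 exclusion and a special COPD rule, which suggests deliberate choice. A reader might see an internal contradiction, or conclude that all any-field categories must be switched to principal diagnosis. Neither follows. A principal-only rule would lose admissions driven by a diabetic complication that was coded second, and those may matter in a chronic disease program.

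Third, one might read the rule as counting every admission of anyone known to have a diabetic complication or hepatitis B. It does not: the code must be on the record of that admission.

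Fourth, the propensity score includes target conditions and the 2010 counts of all, unplanned and avoidable admissions, and section 3.2.2 compares participants with themselves. This helps with imbalance, and the 1.22 in step 5 is not a forecast. The protection is partial, because the counts stop at 2010 while enrolment runs to December 2013, so treatment begun later is missed. Matching also does not undo dilution. Standard errors that allow for extra variation would report the lost precision but not restore it.

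The only planned sensitivity analyses of the matched comparison vary the baseline period, so the outcome definition is never tested.

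**Conclusion.** The concern holds as a badly fixed outcome definition, not as a demonstrated bias. Followed literally, sections 1.2 and 3.1 put unrelated and repeated same-day admissions into the primary event rate whenever a listed code is an additional diagnosis in one of five categories. The exposure is greatest for diabetes complications and possible for B18.0 and B18.1.

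The size is unknown. Under the stated assumptions, 0.5% of people could supply 44% to 80% of events, move a true 0.80 to between 0.89 and 0.96, and raise the standard error of the log rate 3.6- to 4.3-fold. If few sessions carry the code, or few such people are in the cohort, the effect shrinks accordingly. The case for acting is that the problem is possible, untested and cheap to close before analysis.

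**What to change.** 1. In section 3.1, exclude from the avoidable count same-day repeat-treatment admissions (such as dialysis) that qualify only through an additional-diagnosis code, and state how these are identified in the APDC.
2. Apply the same rule to the 2010 avoidable-hospitalisation variable in sections 2.2 and 3.2.4 and in the propensity score.
3. Pre-specify a sensitivity analysis of the primary outcome that requires the principal diagnosis in all five any-field categories, ruptured appendix included.
4. Report event counts by category and by principal versus additional field, so that a reader can see how much the rule matters.

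The cost is SAP wording, a recoded event flag and a little more analysis. No new data are needed if admission dates and diagnosis position are in the extract. Fewer events will be counted. Keeping the any-field rule for other admissions in the primary analysis means that complication-driven stays coded second are not lost.

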### 3.2.4 *Adjusted analyses*

Both the before-after and the time-dependent analyses will be performed without and with adjustment. Potential covariates will include LHD, age, gender, aboriginality, ARIA, SEIFA, target conditions, SF1 and previous patterns of service utilisation (number of hospitalisations in 2010, number of unplanned hospitalisations in 2010, number of avoidable hospitalisations in 2010 and number of ED admissions in 2010).

Each potential covariate will first be analysed using a univariate Poisson regression and only those with a univariate p-value smaller than 0.20 will be included in the final model. To avoid problems due to colinearity, in case of two covariates with a Pearson correlation coefficient greater than 0.8, only the one with the smallest univariate p-value will be kept in the final model. For covariates with more than 10% of data missing, we will create a separate category labeled “missing”.

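### The definition of unplanned hospitalisation joins its criteria with OR, so nearly every admission, planned or not, counts as unplanned

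*SAP*

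**What the plan says.** Section 3.1 of the SAP gives a numbered list under "Secondary efficacy outcomes will include". The first item defines unplanned hospitalisations as "hospitalisations that have status of 'emergency' or the mode of separation is not 'Transfer to Palliative Care Unit / Hospice' or any", where the last two words open a third criterion, again joined by OR: "any of the secondary diagnoses are not 'Palliative care '(Z51.5". The SAP contains no other definition and no bracketing that would limit this one.

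The admissions to which the rule applies are not restricted beforehand. Section 1.2 says the admitted-patient dataset holds "every public and private hospital admission" in the state over the study years.

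The concept is used again in three places:
- Section 2.2 describes unplanned admissions in 2010 (number, average stay, bed-days) separately from all admissions.
- Section 3.2.4 lists "number of unplanned hospitalisations in 2010" as a candidate covariate alongside the total number of hospitalisations. Where two covariates have a Pearson correlation above 0.8, only one is kept.
- Section 3.3.1, step 3, puts all the candidate covariates of section 3.2.4 into the propensity score.

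**The concern.** With OR between the criteria, an admission needs to meet only one. The two palliative criteria read like exclusions, but as joined they bring admissions in: anything that does not end in a palliative transfer qualifies, whatever its admission status. Planned surgery, day procedures and other elective stays all become unplanned.

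Three things are at stake:
- The outcome would nearly duplicate all-cause hospitalisation. An effect of the programme on unplanned care would be mixed with planned care.
- The 2010 unplanned count would nearly duplicate the 2010 total. In the adjusted models of section 3.2.4 the 0.8 rule would very likely drop one of the two, and the distinction between planned and unplanned prior use would be lost.
- The propensity model would hold two near-identical counts, and prior emergency admission would not be balanced separately. This reaches the matched analysis, which section 3.3.1 names as the primary assessment of the programme.

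**Working it through.** The SAP states no figure on this point, so there is none to reproduce. The check is one of logic, followed by an illustration of size.

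**Inputs from section 3.1.** A: admission status is emergency. B: the separation is not a palliative or hospice transfer. C: "any of the secondary diagnoses are not 'Palliative care '(Z51.5". The rule is A OR B OR C. C can be read in two ways:
- C1 (literal): at least one secondary diagnosis is something other than Z51.5.
- C2 (charitable): no secondary diagnosis is Z51.5.

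**Truth table.** Emergency (yes/no) × palliative transfer (yes/no) × secondary codes (none, Z51.5 only, Z51.5 plus other, other only) gives 2 × 2 × 4 = 16 profiles. The cells show how many profiles count as unplanned.

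| Profiles | Number | As written, C1 | As written, C2 | A AND B AND C2 |
|---|---|---|---|---|
| Emergency, any transfer status, any codes | 8 | 8 | 8 | 2 |
| Non-emergency, no transfer, any codes | 4 | 4 | 4 | 0 |
| Non-emergency, transfer, no codes | 1 | 0 | 1 | 0 |
| Non-emergency, transfer, Z51.5 only | 1 | 0 | 0 | 0 |
| Non-emergency, transfer, Z51.5 plus other | 1 | 1 | 0 | 0 |
| Non-emergency, transfer, other only | 1 | 1 | 1 | 0 |
| **Total** | **16** | **14** | **14** | **2** |

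Under either reading, all four non-emergency profiles without a transfer qualify through B alone. All eight emergency profiles also qualify, so the palliative terms remove no emergency admission.

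**Would a smaller repair do?** Changing only the second OR gives A OR (B AND C2), which accepts 8 + 2 = 10 of 16 and still counts planned, non-palliative admissions. The first OR has to change as well. Changing both to AND but keeping C1 accepts 2 of 16, but the wrong two: it keeps an emergency admission coded Z51.5 plus something else, and drops an emergency admission with no secondary code. The wording of the third criterion therefore has to change too.

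**Share of admissions captured.** Profiles are not equally frequent, so 14 of 16 is not a share of admissions. Assumed values, none from the SAP: emergency 30–60% of admissions, palliative transfer 0.2–3%, Z51.5 coded 1–5%.
- Using C2 and independence, the excluded share is (1 − emergency) × transfer × Z51.5. At its largest this is 0.70 × 0.03 × 0.05 = 0.00105, so about 99.9% or more of admissions count as unplanned.
- Under either reading, an excluded admission must end in a palliative transfer. With transfers at no more than 3%, at least 97% count whatever the overlap.
- Under A AND B AND C2 with independence, the share runs from 0.30 × 0.97 × 0.95 = 0.276 to 0.60 × 0.998 × 0.99 = 0.593, which is close to the emergency share.

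**Inflation and dilution.** Let p be the planned share of admissions (assumed). Ignore the few palliative records, and take a rate ratio of 0.85 on unplanned and 1.0 on planned admissions (both assumed). Inflation is 1/(1 − p). The apparent rate ratio is (1 − p) × 0.85 + p.

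| p | Inflation | Apparent rate ratio |
|---|---|---|
| 0.30 | 1/0.70 = 1.43 | 0.70 × 0.85 + 0.30 = 0.895 |
| 0.50 | 1/0.50 = 2.0 | 0.50 × 0.85 + 0.50 = 0.925 |
| 0.60 | 1/0.40 = 2.5 | 0.40 × 0.85 + 0.60 = 0.940 |

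**The case against.** The logical fault itself is hard to defend. The case on the other side concerns its weight.

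- **It is a secondary outcome.** The primary outcome, avoidable hospitalisations, has its own definition by diagnosis codes and is not altered. The SAP numbers its five secondary outcomes but states no hierarchy among them. This stands. The primary comparison is touched only through one of four prior-use covariates.
- **The covariate damage is limited.** The 0.8 rule belongs to the adjusted models of section 3.2.4. Section 3.3.1 carries both counts into the propensity score. Emergency department admissions in 2010 are also a covariate and capture part of prior acute use. Nothing in the SAP shows that a correctly defined unplanned count would stay below the 0.8 threshold. This stands, and the loss of confounder information cannot be quantified from the document.
- **The dilution figures are illustrative.** They depend on assumed planned shares, an assumed 0.85 and no effect on planned admissions. If the programme changed planned admissions, the apparent ratio could move either way. This stands.
- **The intent is inferred.** The SAP does not say whether either palliative marker alone should exclude an admission, or only both together. This stands, and the authors must settle it. On both versions emergency status is required, so neither rescues the text as written.

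**Conclusion.** The definition is wrong as written. It counts every planned admission that does not end in a palliative transfer, under either reading of the third criterion, and nothing elsewhere in the SAP corrects it. That almost every admission is counted requires only that non-emergency palliative transfers be rare. The inflation of about 1.4 to 2.5 times, and the shift of a true 0.85 to between 0.895 and 0.940, rest on assumed planned shares of 30–60% and no effect on planned care, so they show the scale rather than estimate it.

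This is probably a drafting slip. Even so, a programmer who follows the text builds the wrong variable, and one who guesses the intent departs from the plan. It needs correcting before analysis because it affects a named efficacy outcome and the baseline counts used for adjustment and matching. The definition of the primary outcome is unaffected.

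**What to change.** Have the authors confirm the intended logic, then replace the sentence in section 3.1. The likely intended version is: an admission is unplanned if its status is emergency AND its mode of separation is not a transfer to palliative care or hospice AND none of its secondary diagnoses is Z51.5. The new sentence should:
- use AND in both places;
- say that none of the secondary diagnoses is Z51.5, in place of "or any of the secondary diagnoses are not";
- state whether one palliative marker is enough to exclude an admission or both are needed.

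Apply the same definition to the 2010 unplanned counts, stays and bed-days in section 2.2, to the covariate in section 3.2.4 and to the propensity score in section 3.3.1. The cost is one sentence in the SAP and the matching change to the derivation. It needs no data beyond the fields the definition already uses.

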#### *Propensity scoring and matching*

Using baseline characteristics, we will calculate a propensity score defined as the probability of getting enrolled in the program. Matched controls will be selected from the APDC dataset using individuals who never got enrolled into the program. We will follow the following steps:

- Step 1:** Group program participants by period (e.g. month/quarter/semester) according to their enrolment date (the final “grouping period” will depend on the number of participants recruited).
- Step 2:** For each stratum/period, obtain details of the latest hospitalisation occurring in the 12 months preceding the period. Any program participant with no hospitalisation in the preceding 12 months will be excluded from propensity-based analyses.
- Step 3:** Within each stratum/period, calculate propensity score using a logistic regression modeling the probability of getting enrolled in the program. Covariates will include all variables considered for adjusted analyses.
- Step 4:** Within each stratum/period, starting with the earliest period, match 2 non-CDMP participants for each CDMP participant on the propensity score using optimal matching procedures. A control which has been used as a match in an earlier period is no longer available as match for a future period.
- Step 6:** Check the quality of the matching by plotting the propensity score distribution between the cases and controls overall and by period and by calculating the standardised difference for every covariate included in the propensity score calculation.

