#### *Analysis of matched data*

The matched set will be analysed using Poisson regression with generalized estimating equations to account for the matched-nature of the data. The outcome will be the event rate (e.g. rate of avoidable hospitalisations) occurring after the “matching-period”.

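### The re-admission outcome is defined by timing alone, so planned repeat admissions count, and stays continued after an inter-hospital transfer probably do too

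*SAP*

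**What the plan says.** SAP section 3.1 lists five secondary efficacy outcomes. The second is "Hospital re-admissions defined as admissions occurring less than 30 days after discharge". That is the whole rule: it sets a time window and nothing else. It does not restrict the urgency of the second admission, the type of index stay or the way the index stay ended.

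The admissions come from the source described in section 1.2: "The APDC dataset will contain every public and private hospital admission" in NSW from January 2007 to December 2013. No section excludes planned stays or joins adjoining records into a single stay.

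The first secondary outcome, unplanned hospitalisations, shows which other fields are available. It uses an emergency status, and it also uses a condition that "the mode of separation is not" a transfer to palliative or hospice care. The re-admission rule uses neither field.

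For the matched comparison in section 3.3.1, "The matched set will be analysed using Poisson regression with generalized estimating equations to account for the matched-nature of the data". What is modelled there is a rate of events following the matching period, so the program effect on re-admissions would be read as a rate ratio.

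**The concern.** An analyst who follows section 3.1 literally has a complete rule, and that rule gathers three kinds of event:

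- returns to hospital after the patient has gone home;
- scheduled repeat admissions, each of which counts if it starts less than 30 days after the previous discharge;
- probably, the second part of a stay that continues at another hospital.

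The third kind is not a return to hospital in the ordinary sense. The second kind is a return, but a planned one, and a disease-management program need not affect it as it affects unplanned returns. A single rate ratio over all three averages possibly different effects, weighted by shares that the SAP does not give. A reader of the result could not tell whether a ratio near 1 meant no effect on returns to hospital or a real effect mixed with events that the program did not change.

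**Working it through.** **What the text supports**

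1. *Planned admissions.* The rule has no urgency condition and the source has no exclusion. A scheduled series less than 30 days apart is counted from its second admission on. This follows directly from sections 1.2 and 3.1.
2. *Transfers.* Section 3.1 shows that mode of separation has at least one transfer value, so a transfer is one way in which a recorded hospitalisation ends. Section 1.2 covers public and private hospitals, and no rule joins records. The stay at the receiving hospital would then probably be a new admission on or near day 0. This is an inference: the only transfer value named is the palliative one, and the SAP does not say how other transfers are recorded.

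**Size**

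The SAP states no re-admission rate, effect size, alpha or power for this outcome, so there is no figure to reproduce. What follows is an illustration on assumed inputs:

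- *RR*: true rate ratio on the other re-admissions, assumed 0.80;
- *f*: share of counted control re-admissions that are transfers or planned stays, assumed 10% to 40%;
- *g*: the program's rate ratio on those stays, varied because the SAP does not inform it.

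Observed ratio = (1 − *f*) × *RR* + *f* × *g*.

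With *g* = 1 and *f* = 0.10: 0.90 × 0.80 + 0.10 × 1 = 0.82. With *f* = 0.40: 0.60 × 0.80 + 0.40 × 1 = 0.88.

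| Effect on transfers and planned stays | f = 10% | 20% | 30% | 40% |
|---|---|---|---|---|
| g = 1.0 (unchanged) | 0.82 | 0.84 | 0.86 | 0.88 |
| g = 0.8 (same reduction) | 0.80 | 0.80 | 0.80 | 0.80 |
| g = 1.2 (increase) | 0.84 | 0.88 | 0.92 | 0.96 |
| g = 0.7 (larger reduction) | 0.79 | 0.78 | 0.77 | 0.76 |

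With a weaker assumed true effect the direction can reverse. For *RR* = 0.90, *g* = 1.2 and *f* = 40%: 0.60 × 0.90 + 0.40 × 1.2 = 1.02.

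**Power in the unchanged case (g = 1)**

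The plan is to "match 2 non-CDMP participants for each CDMP participant on the propensity score using optimal matching procedures". I therefore took 1:2 allocation, a Wald test on the log rate ratio, an assumed two-sided 0.05 and no overdispersion:

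power = Φ( |log observed ratio| / √(1/E₁ + 1/E₀) − 1.96 ),

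where E₁ and E₀ are the program and control event counts. Power is 80% with transfers and planned stays excluded when the control count is 2 × 275.9 = 551.7 and the program count is 0.80 × 275.9 = 220.7.

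Adding the other stays at share *f* adds 275.9 × *f*/(1 − *f*) events to the program count and twice that to the control count. Power becomes about 76%, 70%, 64% and 57% for *f* = 10%, 20%, 30% and 40%. The extra events narrow the standard error, but not by enough to offset the ratio's move toward 1.

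**The case against.** The strongest reply is that all-cause re-admission is a coherent measure of hospital use. The SAP uses unplanned as a separate label for outcome 1 and does not attach it to outcome 2. It states no purpose for outcome 2, so a reader who takes it as a measure of failed discharges is adding something the document does not say. This stands. Replacing the outcome with an emergency-only one would be a choice of a different outcome, not the correction of an error.

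A reader might also infer that the rule must dilute any program effect. The document does not support that. Attenuation needs the program to leave transfers and planned stays roughly unchanged. If they fall in proportion there is no bias, and if they fall by more the effect is exaggerated.

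Nor does the SAP establish that every inter-hospital move opens a new record. It names one transfer value, and it uses both separation and discharge without equating them. The records might be joined during data preparation described elsewhere. That possibility limits confidence in the transfer part. It does not repair the rule, because no wording in the SAP tells the analyst to count joined stays or points to such a step.

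The illustrative shares and ratios have no source in the SAP, so they cannot rank the problem by size. The planned-admission part survives all of this, since it follows from the wording alone. An all-cause measure also still needs a statement on transfers, because a continued stay is not a return to hospital under any reading.

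**Conclusion.** The point holds in a limited form. The definition counts planned repeat admissions by its plain terms and probably counts continued stays after a transfer, so the rate ratio for this outcome would not isolate true returns to hospital.

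The direction and size of the bias cannot be derived from the SAP. The attenuation from 0.80 to between 0.82 and 0.88, with 80% power falling to between about 76% and 57%, rests on three assumptions: a true ratio of 0.80, a 10% to 40% share, and no program effect on those stays. The power figures also assume no overdispersion.

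This is one of five secondary outcomes. The definition of the primary outcome, avoidable hospitalisations, is unaffected. The change is worth making because it is cheap and because fixing the definition before the analysis prevents a choice between versions once results are known.

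**What to change.** In SAP section 3.1, secondary outcome 2:

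1. Join contiguous records linked by a transfer into one stay before counting re-admissions. State which mode-of-separation values and what gap between records count as a link. If another document already does this, cite it.
2. Measure the less-than-30-day window from the end of the joined stay.
3. Report two rates side by side: all-cause re-admissions, and re-admissions with emergency status.
4. State in advance which of the two is the main version.

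For the second rate, use the emergency status field directly and do not cross-refer to outcome 1. The conditions in outcome 1 are joined by an or, so they also take in admissions without emergency status.

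The cost is a few lines of wording and one data step on fields the plan already uses. The downside is fewer counted events: joining removes some from both rates, and the emergency-status rate is smaller again.
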